## Abstract

**Background:**

Corticosteroids and calcineurin inhibitors (CNIs) are included in renal transplantation immunosuppressive protocols around the world. Well-known side effects are associated with the use of these drugs, including new onset of diabetes after transplantation (NODAT). Long-term patient survival rates are lower among patients with NODAT. The optimal immunosuppressive protocol would therefore include not using corticosteroids and minimization of CNI use.

**Methods/Design:**

This is a prospective, multi-centre, controlled, randomized, parallel group, open-label study involving kidney transplant patients. The study compares a steroid-free immunosuppressive protocol (study arm A), which is based on low-dose tacrolimus and mycophenolate mofetil (MMF) maintenance therapy together with antithymocyte globulin (ATG) induction, with the conventional immunosuppressive protocol (study arm B), being based on low-dose tacrolimus, MMF and steroids together with interleukin-2 receptor (IL2-R) induction. The study is designed to include most normal-risk patients. It will exclude patients seen as at a high risk of rejection. The primary objective of the study is to assess the cumulative incidence of NODAT in the two study arms 12 months after transplantation using the American Diabetes Association type 2 diabetes diagnostic criteria. The composite measure of freedom from acute rejection, graft survival and patient survival will be evaluated. Renal function and chronic changes in the transplanted kidney will be assessed.

**Discussion:**

If this study confirms conceptual expectations, namely decreased incidence of NODAT, the steroid-free study protocol could be used with all patients. The regimen could be especially beneficial for patients at a high risk of diabetes mellitus.

**Trial registration:**

Trial registration: EudraCT 2012-000451-13.

## Background

Corticosteroids and calcineurin inhibitors (CNIs), such as tacrolimus and cyclosporine, are the main ingredients in immunosuppressive renal transplantation protocols throughout the world. These drugs have recognized side effects, such as nephrotoxicity, an increased incidence of diabetes, cardiovascular morbidity and malignancy. New immunosuppressive drugs, such as mycophenolate mofetil (MMF) and interleukin-2 receptor (IL2-R) antibodies now make it possible to reduce, withdraw or avoid corticosteroids or CNIs in many protocols [1]. Steroid-free protocols can now be used safely, providing that a standard trough level of tacrolimus is achieved and combined with MMF and IL2-R antibodies [2]. Doses of CNIs can also be reduced safely, as recently shown in the large Symphony trial, in which the best graft function was achieved in the study arm that used low-dose tacrolimus [3]. However, as in most other CNI-minimization protocols, corticosteroids were not discontinued.

New onset of diabetes after transplantation (NODAT) is associated with increased graft failure and mortality due to cardiovascular events [4]. Long-term patient survival is lower for patients with diabetes mellitus or NODAT when compared with non-diabetic patients [5]. The incidence of NODAT is variously described as reaching from 14% ten weeks after renal transplantation [6] to 37% one year after transplantation [7], and NODAT has been a constant challenge in tacrolimus-based immunosuppression since the drug was first introduced. The incidence of NODAT has decreased as tacrolimus doses have been reduced; but the incidence still seems to be higher than for cyclosporine-based regimens. The DIRECT study showed that the risk of NODAT or impaired fasting glucose is common in CNI-based regimens but is significantly lower with cyclosporine than with tacrolimus in the first 6 months post-transplant [8]. This is one reason cited by transplantation physicians as to why they use cyclosporine rather than tacrolimus with post-transplant patients perceived to be at risk of diabetes. As tacrolimus is a staple drug in modern immunosuppression [3], efforts to reduce NODAT rates have focused on steroid withdrawal. As corticosteroids induce insulin resistance, minimization is also likely to reduce NODAT.

The CARMEN study group reported a significant reduction of NODAT (0.4%) in a steroid-free arm when compared with a 5.4% rate for NODAT in a control arm [2]. The steroid-free arm used daclizumab, tacrolimus and MMF, while the control arm used tacrolimus, MMF and steroids, without IL2-R antibody induction. In contrast, other studies have proposed that basiliximab, also an IL2-R antibody, impaired glucose homeostasis and was associated with an increased risk of NODAT [9,10].

Antithymocyte globulin (ATG) has long been used as a potent induction agent in organ transplantation. It has been used in steroid-free [11,12] and CNI-minimization protocols [13]. To better reduce side effects and toxicity, the optimal immunosuppressive protocol would include both avoidance of corticosteroids and minimization of CNIs. No such protocols have appeared in the literature or been otherwise described. A future protocol, designed to avoid rejections due to inadequate immunosuppression will need to replace corticosteroids or CNIs by increasing or optimizing other immunosuppressive strategies. We believe that the use of ATG induction, instead of IL2-R antibodies, along with the use of therapeutic drug monitoring of MMF, would fit into such a protocol.

The proposed study aims at addressing both the diabetogenic side effect of CNIs and corticosteroids as well as the cardiovascular side effects of corticosteroids in an avoidance protocol.

## Methods/Design

This is a prospective, multi-centre, controlled, randomized, parallel group, open-label study of participants who are enrolled in kidney transplant programmes. The study is comparing a steroid-free immunosuppressive protocol based on low-dose tacrolimus and MMF maintenance therapy together with ATG induction (study arm A) with a conventional immunosuppressive protocol based on low-dose tacrolimus and MMF and steroids together with IL2-R induction (study arm B). The study design is illustrated in Figure 1.

**Figure 1 F1:**
[figure not shown]
**Treatment and follow-up schedule in the SAILOR-study.** ATG, antithymocyte globulin; AUC, area under the plasma concentration time curve; IL2-R, interleukin-2 receptor; mGFR, measured glomerular filtration rate; MMF, mycophenolate mofetil; oGTT, oral glucose tolerance test; Tx, transplant.

Prior to transplantation, a representative group of 222 *de-novo* kidney transplant recipients will be randomized to either of the two study groups (111 in each group) after signing an informed consent agreement. Assignment of subjects to treatment groups will be stratified by donor status (living versus deceased) and by centre.

Enrolment will continue until the required sample size has been randomized. An enrolment time of 36 months is expected.

The study includes persons above 18 years of age who are receiving a first or second single kidney transplant from a deceased or living donor and who are considered able to benefit from a standard immunosuppressive protocol. The study participants are able to give written informed consent and each individual will need to agree to participate in the study for 24 months.

Patients will be excluded from participation if they: (1) already have a diagnosis of diabetes mellitus or have a plasma glucose level of >11.1 mmol/l at admission; (2) are receiving steroids at the time of transplantation; or (3) are likely to need steroids after transplantation. Recipients of multiorgan transplants, those previously transplanted with any other organ than a kidney, or prospective study participants with a complement dependent cytotoxicity panel reactive assay >25% in their most recent tests are also excluded from the study. If the responsible investigator considers the study candidate, for any other reason, to be at a high risk of rejection (which requires enhanced immunosuppression) then the candidate will be excluded. Patients receiving a renal transplant from a human leucocyte antigen (HLA) identical sibling and patients who are recipients of ABO-incompatible kidney transplants will also be excluded from the study.

### Sample size calculation

In two recent phase 3 studies with tacrolimus, steroids and MMF [7], the proposed definition of NODAT gave an incidence rate of 36%. It is reasonable to estimate that a steroid avoidance regimen can reduce the incidence of NODAT to half of that rate. A changed induction regimen (Thymoglobulin rather than Simulect) is expected to reduce the number of rejections. As described earlier, the frequency of rejections has a positive correlation with the incidence of NODAT.

We predict that the percentage of subjects who reach the endpoint of NODAT after 12 months will be 18% in the study group arm and 36% in the control group arm.

Based on this assumption, 222 subjects are required for randomization to the two treatment groups in a 1:1 ratio (steroid-free: steroids) to achieve 80% power for the superiority comparison (Fisher’s exact test) on the intention-to-treat population of the primary endpoint between the two treatment groups, with a two-sided type I error of 5% and allowing for a 5% drop-out rate.

### Randomization and treatment

The study participants will be randomized before transplantation to one of the two following treatment arms using a 1:1 relation from an internet-based system.

Study arm A: the steroid-free low-tacrolimus study arm will receive Thymoglobulin® induction (2.5 mg/kg, pre-or peri-operatively on day 0 and 2.5 mg/kg on day 1) and maintenance therapy of Advagraf® with an initial preoperative dose of 0.1 mg/kg followed by 0.2 mg/(kg.day) orally in one dose (concentration: 5 to 10 ng/ml; after 3 months, 4 to 7 ng/ml); and MMF 1gx2 started preoperatively, controlled by a single AUC (area under the plasma concentration time curve) measurement, on day 10 ± 5 days, with a target AUC of between 40 and 60 (mg.h)/l). To diminish ATG side effects, 250 mg methylprednisolone will be given before ATG infusion on day 0 and 50 mg will be given before ATG infusion on day 1.

Study arm B: the standard low- tacrolimus study arm protocol consists of Simulect® induction 20 mg intravenously (day 0 and day 4) and maintenance immunosuppression with an initial preoperative dose of 0.1 mg/kg followed by Advagraf® 0.2 mg/(kg.day) orally in one dose (concentration: 5 to 10 ng/ml) and after 3 months (4 to 7 ng/ml). MMF 1gx2 is started preoperatively (controlled by a single AUC measurement, on day 10 ± 5 days, with a target AUC between 40 and 60 (mg.h)/l) and steroids are added according to hospital practice, but not less than 5 mg prednisolone daily after 6 months.

### Trial organization

Called the SAILOR-study, this is an investigator-initiated trial. Preliminary investigator meetings were organized by Sahlgrenska University Hospital, the sponsor of the study. Two Swedish transplant centres (Gothenburg, Malmö) and one Danish centre (Aarhus) are participating in the study.

Study drugs will be purchased by the participating hospitals. The investigation medicinal products will be exempt from the EU Clinical Trials Directive as they will be used within the terms of their marketing authorization. All treatments will be on an open-label basis.

Before recruitment commenced, the sponsor visited all sites to train relevant staff in the study procedures. The sponsor will closely monitor recruitment rates and the completeness of follow-up data. Sites will be monitored during recruitment and follow-up through a combination of on-site visits and central statistical monitoring.

A data monitoring committee (DMC) will be appointed. An independent group, outside the sponsor and steering group, will have this responsibility. The DMC will consist of one or two physicians and one statistician; none will have any other involvement with the study. For efficacy, the DMC should use O’Brian-Fleming group sequential boundaries. The DMC should also look for safety and conditional power when giving advice regarding continuation of the study. The DMC should start to look at the data after 40% of the subjects have completed the study.

The work of the DMC will be defined in a DMC charter. The sponsor and DMC members, before their first look at the data, should sign off this document when 40% of the subjects have completed the study.

The Regional Ethical Review Board in Sweden and Denmark have approved the study. To protect participants, the study was designed to comply with the World Medical Association’s current Declaration of Helsinki on ethical principles of human experimentation.

The most relevant safety parameters assessed within this study are incidence of diabetes mellitus, acute rejection, renal function, loss of graft, incidence of cardiovascular complications and events or incidence of malignancy. Data on adverse events outside these topics will not be collected.

Adverse events are recorded in the study’s case report form. Serious adverse events are recorded in the case report form, on a serious adverse events worksheet and in the participant’s separate medical record.

The Transplant Institute, Gothenburg will be responsible for all statistical programming and analysis, as well as statistical quality control and validation of programming and statistical analysis. The responsible biostatistician will coordinate the statistical analysis.

A detailed description of all the statistical analyses of all efficacy and safety variables together with an overview of tables and figures will be given in a separate statistical analysis plan. The plan will be finalized before the database of the study is locked. Any deviations from the plan will be justified in the clinical study report.

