## Discussion

This controlled study was designed to evaluate whether a steroid-free, low-dose CNI protocol based on tacrolimus, induction with a high-bolus dose of ATG and therapeutic drug monitored MMF, may be used without reduction in efficacy or safety and with side effects minimized. The protocol is to be compared with a low-dose CNI (tacrolimus) protocol with steroids and IL2-R inhibitor for induction.

Calcineurin inhibitors lower insulin secretion while steroids contribute to insulin resistance. The β cell toxic effect when tacrolimus is used is, however, dose-dependent and reversible [16]. If the tacrolimus concentration is kept low, the risk for diabetes can be minimized [17]. The difference between tacrolimus and cyclosporine in lowering insulin secretion has been shown to be present only very early after transplantation, but not later on [18]. The Symphony study sub-analysis describes no significant difference in fasting glucose between low-tacrolimus protocol and both cyclosporine protocols [19]. In the FREEDOM trial, which used a cyclosporine-based regimen, the *de-novo* use of antihyperglycemic medication was reduced from 14.7% to 4.5% when steroids were avoided [20]. While diabetogenic effects of steroids and CNIs are well documented, the role of IL2-R inhibitors in impairment of glucose homeostasis have been discussed, but the results are controversial [9,10].

The incidence of NODAT is dependent on how it is defined. Using the American Diabetes Association definition of NODAT, we are expecting rates above 30% in the steroid arm. We have not included HbA1c in diagnostic endpoints for NODAT, as it could be affected in early transplant period by anemia, uremia and erythropoietin usage [21].

With early steroid withdrawal, one retrospective study describes less rejection with ATG induction when compared with IL2-R antibody blocker use [12]. Usually, the drug is administered for 7 to 10 days after transplantation. There is, however, clinical [22] as well as experimental [23,24] evidence that suggests that a single high-bolus dose of ATG given just before transplantation has a similar effect; a dose might even have tolerogenic properties. In a large single-centre cohort, post-transplant diabetes was significantly reduced when steroid-free immunosuppression was given and the frequency in the steroid-free group was only 1% after 1 year [25].

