Dosing of MMF may be optimized by increasing the initial dose [26], and by the use of therapeutic drug monitoring by estimated AUC measurements [27]. Optimized usage of MMF can also reduce the risk of rejection in a steroid avoidance regimen.

In the experimental arm, participants will receive a more powerful induction treatment (Thymoglobulin); however, they will not receive steroids. We do not expect the experimental arm to be less effective in preventing rejection and we expect that the steroid-free regimen will reduce the rate of diabetes.

Study patients will undergo a biopsy after 1 year. Biopsies are frequently performed, but not on all patients outside a study. The risk for bleeding after biopsy is low but sometimes a short period of haematuria is observed. Evidence is increasing that surveillance biopsies not only give information on acute rejection and chronicle changes but also add other important information for the care of the individual being treated [28,29]. An evaluation of implantation biopsies will help to distinguish donor-related changes from recipient-related processes.

Study participants will also undergo an oral glucose tolerance test, which is not associated with any side effects, other than the discomfort of drinking a strongly sweet fluid.

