If this study confirms the conceptual expectations, namely a decreased incidence of NODAT, the steroid-free study protocol could be implemented among all study participants. The regimen could be especially beneficial among those with a high risk of diabetes mellitus or significant cardiovascular complications and among those with obesity, psychiatric conditions or skeletal demineralization. Implementation, of course, has to be balanced with a theoretically higher risk of rejection; the maintenance therapy is limited to two drugs and could be considered weaker than the conventional triple regime. A stronger induction therapy, with potential tolerance-induced effect, is used to compensate for the lessened maintenance immunosuppression. Signs of early acute rejection will not be the only function monitored; chronic changes, low-grade humoral rejection in protocol biopsies at 1 year and any development of donor-specific HLA antibodies will also be closely observed, to detect any sign of long-term under-immunosuppression. The current study has a two-year follow-up period and, therefore, cannot give answers concerning long-term patient and graft survival. We will consider extending the follow-up period to 5 years if the outcome is as expected.

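### Adverse events outside six listed topics are not collected, so the arms cannot be fully compared on induction-related harm, and the stated safety aim can be only partly answered

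*Protocol article*

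**What the plan says.** All of this is in the protocol article.

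- **Trial organization, the list.** "The most relevant safety parameters assessed within this study are incidence of diabetes mellitus, acute rejection, renal function, loss of graft", followed by "incidence of cardiovascular complications and events or incidence of malignancy".
- **Trial organization, the exclusion.** "Data on adverse events outside these topics will not be collected". No exception is attached.
- **Trial organization, serious events.** In the next paragraph: "Serious adverse events are recorded in the case report form, on a serious adverse events worksheet and in the participant’s separate medical record". The sentence gives the places of recording. It does not say whether the six-topic limit applies to serious events.
- **Trial organization, data monitoring committee.** The committee is asked to consider safety, as well as efficacy boundaries and conditional power, starting once 40% of subjects have completed the study.
- **Randomization and treatment.** Arm A receives Thymoglobulin and arm B Simulect. For arm A: "To diminish ATG side effects, 250 mg methylprednisolone will be given before ATG infusion on day 0", with a further dose before the day 1 infusion.
- **Discussion.** The study was designed to evaluate whether the regimen "may be used without reduction in efficacy or safety and with side effects minimized". The same section describes arm A's induction as the more powerful of the two.

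**The concern.** The arms differ in two ways: arm A drops steroids and also has a different induction agent. The protocol expects side effects from that agent, because it premedicates against them, yet it closes the list of recorded events without any topic under which infusion reactions, infections or low blood counts would fall.

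An analysis plan cannot repair this later, because it can only analyse what was collected. If NODAT falls in arm A and the six topics look similar, the report may say that safety was preserved and side effects minimized, with part of the evidence needed for that statement missing by design. The monitoring committee would advise on continuation with the same gap. The Discussion foresees wide use of the regimen if the result is favourable, and weighs that use only against rejection.

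**Working it through.** The point rests on the text, so the main check is a comparison of statements. A short calculation then shows what collection would yield.

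**1. Is any induction-related event covered elsewhere?** Objectives and endpoints adds patient survival, antibody-mediated rejection, donor-specific antibodies, measured GFR, biopsy changes, hypertension, and antihypertensive and lipid-lowering drugs. None of these is an infection, blood-count or infusion outcome. An event that ends in death or graft loss is counted, but as a death or a graft loss.

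**2. The two readings of Trial organization.**

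| Reading | Non-serious event outside the six topics | Serious event outside the six topics |
|---|---|---|
| Exclusion applies to all adverse events | not collected | not collected |
| Serious events are recorded whatever the topic | not collected | collected |

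The first column is the same under both readings, so some induction-related harm is always lost. The second column depends on a scope that the text leaves open. Three centres in an open-label trial could resolve it differently.

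**3. Is the primary analysis touched?** No. The planned size comes from NODAT rates of 36% and 18%. A two-proportion calculation with continuity correction gives 106 per arm, and 106 × 1.05 = 111.3, in line with the stated 111 per arm. Exact Fisher power is 81.2% at 106 per arm and 82.9% at 111. The stated 222 reproduces and does not depend on adverse event collection.

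**4. What would collection give?** The documents state no rates for the uncollected events, so those below are assumptions, shown over a range. The 95% half-width for a difference between arms is 1.96 × √[(p₁(1−p₁) + p₂(1−p₂)) / n]. At the end of the trial n = 111 per arm. At the first monitoring look, 0.40 × 222 = 88.8 completers, about 44 per arm.

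| Assumed rates | Sum of p(1−p) | n = 111 | n = 44 |
|---|---|---|---|
| 5% vs 15% | 0.0475 + 0.1275 = 0.1750 | ±7.8 points | ±12.4 points |
| 20% vs 30% | 0.16 + 0.21 = 0.37 | ±11.3 points | ±18.0 points |
| 30% vs 45% | 0.21 + 0.2475 = 0.4575 | ±12.6 points | ±20.0 points |

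For rarer events, 1 − 0.05^(1/111) = 0.027: an event type with a true frequency of 2.7% in an arm has a 95% chance of appearing at least once among 111 patients. Under the exclusion, an event type that falls outside collection yields neither an estimate nor a signal.

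**The case against.** **The limit is open and deliberate.** The products are used within their marketing authorization, the ethics boards approved the study, and the exclusion is stated plainly. That stands as a reason why collection was kept short. It does not remove the conflict with the Discussion's aim. The Background says that no protocol combining steroid avoidance with CNI minimization has been described, so authorization of the single drugs does not settle the safety of the combination.

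**The aim is a Discussion sentence, not a listed objective.** This is correct, and the listed objectives remain assessable. It supports saying that the aim cannot be fully answered. A reader might infer that the trial cannot answer its safety question at all; that goes too far, because the six topics are still compared.

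**Serious events may all be recorded.** They may. A reader might infer that serious infections would never be recorded or never reach the monitoring committee, or that the serious-event sentence flatly contradicts the exclusion. The text supports neither: it leaves the scope open.

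**The list may look tilted towards arm A.** A reader might infer this, but the documents do not bear it out. Acute rejection, graft loss, renal function and malignancy are all listed and can count against arm A. Donor-specific antibodies and one-year biopsies add to that.

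**The precision is modest.** For 20% versus 30%, the interval at 111 per arm runs from about −1 to +21 points and includes zero; at the first look it is wider, although more patients may have been randomized by then. This stands. Collection would give an estimate and a signal, not a confirmatory safety test.

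**The documents do not name these events.** They speak only of ATG side effects in general. Choosing infection, blood-count and infusion events is therefore a judgement for the investigators to confirm. The conflict itself does not depend on the exact list.

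**Possible benefit in "obesity, psychiatric conditions or skeletal demineralization".** A reader might ask for these outcomes too. The Discussion offers them as conditional speculation about future use, not as an objective, so no such demand follows.

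**Conclusion.** The point holds in limited form. The exclusion is a fixed rule, not a detail left to another document. Taken as written, it conflicts with the Discussion's safety aim, with the induction side effects that the protocol itself anticipates, and with the monitoring committee's safety task. Non-serious events outside the six topics are lost under any reading; serious ones are lost as well if the exclusion governs them.

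The consequence is confined to what the trial may conclude about safety: the comparison of induction-related harm is incomplete. The forgone information is an estimate good to about ±8 to ±13 points at full size, on assumed rates of 5% to 45%. NODAT at 12 months, its analysis and the sample size are not affected. This is a low-cost improvement that should be made, not a flaw in the primary result.

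**What to change.** Replace the exclusion sentence in Trial organization with text such as:

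> All serious adverse events, whatever the topic, are collected in both arms. The following are also collected in both arms, whether serious or not: infections needing treatment or hospital admission, leucopenia or thrombocytopenia, and infusion reactions to induction. These events are included in the safety tables for the data monitoring committee, together with the safety parameters listed above.

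This settles the scope of serious-event recording and closes the gap for non-serious events. The investigators should confirm the list of events of interest. The article refers to the start of recruitment in the past tense, so if patients are already enrolled, the change should take effect in both arms at all three centres on one documented date.

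The cost is modest extra case report form entry. No visit, procedure, treatment or sample size changes.

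If collection is not widened, state explicitly whether serious events outside the six topics are recorded, and narrow the Discussion's safety and side-effect statement to the listed topics. That costs only a wording change, but leaves the comparison incomplete.
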